#### Recruitment {15}

Participants will be recruited from the local limb loss population. The investigators have access to a group of transfemoral amputees who have volunteered to serve as patients for students within the Orthotics and Prosthetics Program at the University of Pittsburgh, as well as participants of previous studies who were identified through support groups and word of mouth. Participants will also be recruited from the clinics of a local physiatrist and the prosthetics and orthotics practice of a collaborating local prosthetist. Further recruitment avenues include the Pitt+Me Research Registry comprising over 117,000 individuals who have volunteered to be contacted for research studies at the University of Pittsburgh, and social media including Facebook.

### Assignment of interventions: allocation

#### Sequence generation {16a}

The order of the modified sockets worn by each participant will be randomized using computer-generated random numbers.

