**Methods:**

Users of transfemoral prostheses will be asked to walk on a treadmill wearing their current socket plus 8 different check sockets with designed changes in different structural measurements that are likely to induce changes in residual limb motion, skin strain, and pressure distribution within the socket. Dynamic biplane radiography and pressure sensors will be used to measure in-socket residual limb mechanics. Patient-reported outcomes will also be collected after wearing each socket. The effects of in-socket mechanics on both physical function and patient-reported outcomes (aim 1) will be assessed using a generalized linear model. Partial correlation analysis will be used to examine the association between research-grade measurements and readily available clinical measurements (aim 2). In order to compare the new quantitative design method to the standard of care, patient-reported outcomes and cost will be compared between the two methods, utilizing the Wilcoxon-Mann-Whitney non-parametric test (aim 3).

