### Interventions

#### Explanation for the choice of comparators {6b}

Every participant in aims 1 and 2 will be fitted with several different check-sockets for this study, each deliberately modifying one of the independent variables: brim height, volume, cross-sectional geometry, and material stiffness. These variables are known to have an effect on the comfort and function of the socket, and they are among those routinely altered in the static and dynamic fitting process [33]. Those modifications are generally iterative and performed in conjunction with others. For instance, changes in the geometry such as the oblique medio-lateral dimension at the perineum by padding the area of the ischial containment level will also affect the volume of the socket as well as the material stiffness in the modified region. The degree of modifications and manner of combinations is very much customized and informed by individual characteristics such as soft tissue content and pain tolerance. For the study, in order to standardize interventions as much as possible and minimize the risk of drastically compromised socket fit, we will make well-defined modest changes using the participants’ original (current) sockets as the baseline. One single prosthetist will facilitate all the modifications to assure consistency across the sample.

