### Outcomes {12}

Outcomes for each participant will be averaged across three trials for each of the interventions, to analyze the change from baseline with different socket designs.

Many of the assessment methods are identical or equivalent to clinical assessment instruments that are associated with high validity and low risk for the target population. The effective radiation dose due to dynamic biplane radiography is estimated to be 2.0 mSv or less for the 27 trials collected for each participant. For comparison, the average effective dose associated with a knee CT scan from our previous studies was 1.4 mSv, and in the USA, we receive about 3.0 mSv of exposure from natural background radiation every year [37].

The following is the primary outcome variable:
*Socket comfort*

The following are the secondary outcome variables:
*Hip range of motion (ROM)**Three-dimensional (3D) skin motion within the socket**Residual femur position within each socket**In-socket pressure**Plantar pressure**Ground reaction forces during gait**Overall body motion (e.g., trunk lean, hip flexion/extension) during gait*

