#### Implementation {16c}

The allocation sequence will be generated by the study statistician who is not involved in the data collection. All participants in either study phase will be enrolled by the study PI and will eventually be exposed to all interventions of the study phase in a randomized sequential order.

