### Data collection and management

#### Plans for assessment and collection of outcomes {18a}

##### PROMs

Participants will be asked to rate their overall perception of the (1) comfort and (2) function of each socket relative to their current socket on a scale ranging from − (a very great deal worse) to 0 (about the same) to 7 (a very great deal better) using a global rating of change scale [38] (GRC). The GRC scale was selected over other questionnaires because, intuitively, it makes sense that a patient’s perception of comfort and function gives a more accurate assessment if a true change has occurred rather than a prognostic rating [39]. The Prosthetic Limb Users Survey of Mobility (PLUS-M) 12-item short form will be collected after wearing of each socket to provide a secondary measure of perceived mobility. In addition, participants will be completing the OPUS device satisfaction survey to establish baseline satisfaction with their current device and the Amputee Mobility Predicter with prosthesis (AmpPro), attached, to assess their mobility level. All of these data will be collected via tablet using the REDCap system, a secure, web-based application designed to optimize data collection. The REDCap system is currently in place and used to collect data for ongoing research studies in the Biodynamics Lab.

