##### Dynamic biplane radiography

Participants will then walk at their self-selected pace which will be held constant by the treadmill while wearing each of the 9 socket designs. We selected walking because it is the most common lower body functional activity, and comfort and function during walking have a major impact on amputee quality of life. After donning the socket, the participant will be allowed time to acclimate to each socket by walking on the treadmill for up to 5 min. After acclimation, we will collect a total of three trials for each of the 9 sockets. We will collect synchronized biplane radiographs for 1 s at 100 images per second to image the residual femur and skin motion within the socket during the late swing through push-off phase of gait. Images will be collected with 1-ms exposures in all cases to minimize motion blur and radiation exposure. Three-dimensional (3D) skin motion within the socket will be determined by tracking the motion of 40 to 50 small metal beads (1 to 2 mm diameter) that will be secured to the skin of the residual limb in a grid pattern before donning the socket (Fig. 2A). Beads will be secured using Quick Grip glue, a type of contact cement that does not permanently bond to the skin like Super Glue but is strong enough to hold the bead to the skin without moving. Residual femur motion will be determined with sub-millimeter accuracy using a validated volumetric model-based tracking process that matches subject-specific bone models obtained from CT to the biplane radiographs [42–44] (Fig. 10).

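### The current socket, the reference for change from baseline, is not placed in the random test order; if it is tested at a fixed position, measured changes are confounded with position

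*Protocol article*

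**What the plan says.** All references are to the protocol article, and the point concerns aims 1 and 2.

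- **Conditions tested.** The abstract has participants "wearing their current socket plus 8 different check sockets". Under Dynamic biplane radiography they walk "while wearing each of the 9 socket designs", and "we will collect a total of three trials for each of the 9 sockets".
- **What is randomised.** Sequence generation {16a}: "The order of the modified sockets worn by each participant will be randomized using computer-generated random numbers". Implementation {16c} adds that participants "will eventually be exposed to all interventions of the study phase in a randomized sequential order".
- **What the reference is.** Explanation for the choice of comparators {6b} makes modest changes "using the participants’ original (current) sockets as the baseline". Outcomes {12} averages three trials per intervention "to analyze the change from baseline with different socket designs".
- **How comfort and function are rated.** Under PROMs, participants give a global rating of change (GRC) for the comfort and "function of each socket relative to their current socket".
- **When testing happens.** Participant timeline {13} describes testing of the socket variants over one or two laboratory visits. It does not place the current socket in that schedule.

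**The concern.** Randomising test order in a within-subject study keeps fatigue, treadmill habituation, limb volume change and skin irritation from lining up with a particular condition. The rule as written gives that protection to the eight check sockets. It does not give it to the ninth condition, which is the one all the others are compared with.

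If the current socket is always tested at the same point in the session, any drift over the session enters each measured difference between a check socket and the current socket. It has the same sign on average for every design, and recruiting more participants does not reduce it. A reader could then take a session effect for an effect of changing the socket.

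**Working it through.** **1. Is the current socket in the random order?**

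- Sections {Modified stiffness}, {Modified brim height}, {Modified volume} and {Modified cross-sectional geometry} describe two variants each: 2 + 2 + 2 + 2 = 8. These are the check sockets. The current socket is the ninth condition, and 9 sockets × 3 trials = 27 trials, the number given in Outcomes {12}.
- {16a} limits the random order to the modified sockets.
- {16c} refers to all interventions of the phase. Strategies to improve adherence {11c} explains, for aims 1 and 2, that the interventions are the modified check sockets, and {6b} calls the current socket the baseline. Read together, {16c} agrees with {16a}, and neither places the current socket in the sequence.
- No section says that the current socket is tested first, last or at any other set position.

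**2. What would a fixed position do?**

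The article has no figure of its own to reproduce here. The following is an illustration. Assume one session with positions 1 to 9 and a linear drift of d per position. Let the current socket be fixed at position k. The positions sum to 45, so:

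- mean position of the eight check sockets = (45 - k)/8
- mean gap, check minus current = (45 - k)/8 - k = (45 - 9k)/8

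| Place of the current socket | Mean gap (positions) | Average shift in a measured change |
|---|---|---|
| First, k = 1 | 36/8 = +4.5 | +4.5d |
| Last, k = 9 | -36/8 = -4.5 | -4.5d |
| Randomised among all nine | 5 - 5 = 0 | 0 in expectation |

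With the current socket first, the gap for one participant and one check socket runs from 1 to 8 positions. Simulation of random orders of all nine gave a mean gap of 0.007 positions with a standard deviation of 3.87. Position noise therefore remains for an individual but is not systematic.

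The value of d is an assumption. At d = 0 there is no shift. At d = 1% of the baseline value per position, the average shift is 4.5 × 1% = 4.5%, and for a single participant and socket it is 1% to 8%.

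**3. Which comparisons are touched?**

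- *Measured outcomes expressed as change from the current socket:* affected if its position is fixed.
- *One check socket against another:* not affected in expectation. With the current socket fixed first, the simulated mean position difference between two check sockets was 0.02.
- *GRC comfort and function:* each is one direct rating against a socket the participant already uses, not a difference between scores taken at two test positions.
- *Aim 1 and aim 2 models {20a}:* these are a generalized linear model of outcomes on in-socket mechanics and partial correlations. Neither is specified as a contrast with the current socket.

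**4. Could analysis alone repair it?**

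Under the linear drift used above, largely yes. The slope can be estimated from the eight check sockets, which are randomised over their own positions, and carried to the position of the current socket. If position effects may take any shape, no: a position held only by the current socket cannot be separated from that socket.

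**The case against.** The strongest reply is that the bias is conditional on something the article never says. No fixed position is stated, {16c} speaks of all interventions, and the walking section treats the nine designs together. The schedule figure is not visible and the full protocol may settle the order. This stands in part. A reader might infer that the current socket goes first, and the article does not support that as fact. It is less convincing as a reading of {16c}, because {11c} says what the interventions are. Nor is this merely a detail left out: {16a} states the scope of randomisation, and that scope omits the reference condition.

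A second reply is that little of the planned inference depends on this contrast. That is largely right. A reader might infer that every change from baseline is biased, including the primary outcome. Socket comfort in aims 1 and 2 is rated directly against the current socket, so that inference fails. Fatigue may still colour the rating of a socket worn late, but the order of those sockets is randomised.

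A third reply is that a position term would deal with the problem. Under linear drift it would, so it would be wrong to say that no adjustment can help. The repair does rest on extrapolating an assumed shape, which randomising the ninth condition makes unnecessary.

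Finally, the size is hypothetical, and testing split over two visits would break the single nine-position session. Both statements are correct.

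**Conclusion.** The point holds in a limited form. The stated rule randomises the modified sockets and leaves the reference for change from baseline outside the sequence, with no position given. If that position is fixed, measured changes from baseline carry an average shift between -4.5d (last) and +4.5d (first). This assumes linear drift within a single nine-socket session and a value of d that the article does not supply. If all nine are randomised, the expected shift is zero.

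The article does not show that bias is present, that the current socket is tested first, or that the comfort ratings, the comparisons among check sockets or the aim 1 and 2 models are compromised. The change is worth making because {12} announces the exposed contrast and closing the gap costs almost nothing.

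**What to change.** - Amend Sequence generation {16a} so that the order of all nine sockets, including the current one, is randomised for each participant. If this is already done in practice, a one-sentence correction is enough.
- Record the test position and visit for every socket, and include position in the analysis of measured changes from baseline.
- For participants already tested with the current socket at a fixed position, keep it as the baseline and adjust for a position trend estimated from the randomised check sockets. State the assumed shape of that trend.
- For those participants, also report change against the unmodified PETG copy, only as a labelled sensitivity analysis. The copy lies inside the random order, but it is itself one of the two stiffness variants and may differ from the current socket in material. It should not replace the baseline or be mixed with it in one analysis.

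The cost is a new random list for the remaining participants, with no extra trials, imaging, sockets or visits. The drawback is one more prosthesis swap when the current socket falls in mid-session.

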### Trial design {8}

The trial design is an exploratory single-group crossover trial (Fig. 6).

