#### Participant timeline {13}

Participants in the first stage (aims 1 and 2) of the study, upon eligibility screening and completing the consent process, will be fitted for a check socket. After 4 weeks, during which time 8 derivatives of the socket will be produced, participants will complete testing with each of those socket variants over one or two lab visits. The participant timeline for the second stage (aim 3) includes clinical testing of one socket variant and spans a larger period (Fig. 8).

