#### Sample size {14}

To facilitate aims 1 and 2, GLM will be utilized, which is a flexible generalization of ordinary linear regression that allows for response variables that have error distribution models other than a normal distribution and is often robust to smaller sample sizes. With a sample size of *n* = 30 at 80% power and *α* = .05, we should be able to detect a moderate-to-large overall model effect (*f*^2^ = 0.45), while including all three in-socket mechanics. We will examine the effect(s) of each in-socket mechanical parameter on outcomes by utilizing the type III sum of squares tables. If our sample size drops below 30, we will develop separate models for each of the parameters of interest and outcome.

For aim 3, in order to compare the two methods of socket design (the quantitative design method compared to standard of care), we will compare patient-reported outcomes and cost between the two methods, utilizing the Wilcoxon-Mann-Whitney non-parametric test. With a sample size of *n* = 15 at 80% power and *α* = .05, we will be adequately powered to detect a moderate-to-large effect (*d* = 0.476) with respect to the differences in patient-reported outcomes and cost by method.

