As part of the pilot clinical trial, we will use empirical data to test the socket modification model(s) created in aim 1 and clinical measure correlations obtained in aim 2. When empirical data are used to evaluate the model, there are several conventional statistical tests that can be applied to test the null hypothesis that the model output is wrong. These involve showing that some form of the predicted value does not equal the same form of the observed value (e.g., typical predicted, typical observed). The simplest empirical comparison is that of a regression of observed values on predicted values. We will obtain data as described for aims 1 and 2 on an additional 15 transfemoral prosthesis users using their current sockets and the sockets designed as part of the standard of care and through the new quantitative design process.

In order to compare the two methods of socket design (the quantitative design method compared to Standard of Care), we will compare patient-reported outcomes and cost between the two methods, utilizing the Wilcoxon-Mann-Whitney non-parametric test. Socket Comfort Scores (SCS, a simple patient-reported comfort score from 0 to 10) will be used to evaluate patient outcomes after wearing the two sockets. The SCS are reported to have a standard deviation of 2.3 points [50], meaning we will be powered to detect a difference of 1.1 points in the SCS given our sample size. With regard to costs, we will compare the two design approaches on the number of visits, cost of materials, and total cost of labor needed to develop the new socket. These costs will be recorded by the study prosthetist in his practice for the standard of care and in the Biodynamics Lab for the quantitative design method.

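### Aim 3 states no balance between the two socket orders, and its method comparison uses neither period nor pairing, so an uneven split of 15 people can shift the estimate and precision is lost

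*Protocol article*

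**What the plan says.** The article calls the design a crossover (Trial design {8}): "The trial design is an exploratory single-group crossover trial". Sequence generation {16a} gives the only mechanism for order: "The order of the modified sockets worn by each participant will be randomized using computer-generated random numbers". That sentence does not name aim 3, and modified sockets is the term used for aims 1 and 2. Implementation {16c} extends random order to both study phases: participants "will eventually be exposed to all interventions of the study phase in a randomized sequential order". The same section has the study statistician generate the sequence.

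For aim 3, Statistical methods {20a} says that comfort scores "will be used to evaluate patient outcomes after wearing the two sockets", so each of the 15 people scores both. The comparison is then fixed: "we will compare patient-reported outcomes and cost between the two methods, utilizing the Wilcoxon-Mann-Whitney non-parametric test". No period or sequence term is named there or in Sample size {14}.

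Other sections point the other way. Participant timeline {13} says that the second stage "includes clinical testing of one socket variant and spans a larger period", and the adherence section {11c} speaks of a single new socket replacing the original.

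**The concern.** In a two-period crossover, anything that changes for everyone between the first and second socket adds to the second-period score whichever method is worn. Examples are getting used to a socket other than the old one, change in the limb, or a second fitting that takes fewer visits. If equal numbers wear each method second, the shift cancels in the mean difference between methods. If not, part of it remains and looks like a method effect. Fifteen people cannot split evenly, and simple randomisation often splits them badly.

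The named test makes no correction. It treats the 30 scores as two independent samples, so it ignores both the order and the fact that each person contributes to both sides. At stake are the comfort and cost estimates from a small pilot, whose single realised split is the one that readers will interpret.

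**Working it through.** **Inputs from the article.** n = 15, α = 0.05, d = 0.476 (Sample size {14}); Socket Comfort Score SD 2.3 and detectable difference 1.1 points (Statistical methods {20a}).

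**Assumptions, not in the article.** Simple randomisation of order; a period shift δ of 0 to 2 points; a within-person correlation ρ of 0.3 to 0.79.

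**1. The plan's own figure.** 0.476 × 2.3 = 1.095, which rounds to the stated 1.1. The 80% power does not reproduce at n = 15. It is 24% for two independent groups of 15 (two-sided t), 39% for a paired Wilcoxon test (two-sided) and 54% for a paired t-test (one-sided). That is a separate point, but it shows that aim 3 has little power to spare.

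**2. How uneven the split can be.** With X ~ Binomial(15, 0.5):
- P(8:7) = 2 × 6435/32768 = 39%
- P(10:5 or worse) = 2 × 4944/32768 = 30%
- P(11:4 or worse) = 2 × 1941/32768 = 12%
- P(12:3 or worse) = 2 × 576/32768 = 3.5%

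**3. How much of a shift passes through.** Write each person's method difference as D = τ + δS + e, with S = +1 or −1 by order. The mean of D is then off by δ(n1 − n2)/15. Averaged over simple randomisation, the absolute share passed on is 21% of the shift and the mean bias is zero.

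**4. Type I error of the named test.** Simulated (40,000 runs) at ρ = 0.5:

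| Split | Share of shift | Bias, δ = 1 | Type I error, δ = 1 | Type I error, δ = 2 |
|---|---|---|---|---|
| 8:7 | 6.7% | 0.07 | 0.7% | 0.5% |
| 10:5 | 33% | 0.33 | 1.4% | 3.1% |
| 11:4 | 47% | 0.47 | 2.3% | 7.6% |
| 12:3 | 60% | 0.60 | 3.7% | 15.9% |

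Over all orders at ρ = 0.5 the named test rejects in 0.7% to 2.4% of null trials for δ from 0 to 2. At ρ = 0.3 and δ = 1 it passes 5% only at 12:3 (5.8%).

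**5. Precision.** The SD of D is 2.3 × √(2(1 − ρ)), or 2.3 at ρ = 0.5, so the SD of the estimated difference is 2.3/√15 = 0.59. Simple order without adjustment adds δ²/15 to the variance:
- δ = 1: √(0.353 + 0.067) = 0.65
- δ = 2: √(0.353 + 0.267) = 0.79

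**6. Power for 1.1 points (simulated).**

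| Analysis | ρ = 0.5 | ρ = 0.79 |
|---|---|---|
| Named test, simple order | about 16% | about 10% |
| Rank test on period differences, 8:7 | about 34%, any δ | about 68%, any δ |

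A signed-rank test with simple order separates the two sources of gain. At ρ = 0.5 it has 39% power with δ = 0, 33% with δ = 1 and 23% with δ = 2. So pairing alone explains most of the gain over the named test. Period adjustment costs about 4 percentage points when there is no shift (39% to 34% before rounding: 38.6% to 34.4%), breaks even near 1 point, and gains about 11 points at 2. The type I error of the period-adjusted rank test is about 4% at 8:7, whatever the shift.

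**The case against.** **Plain randomisation is not stated.** A reader might infer from Sequence generation {16a} that the order is simply randomised. The text does not say so: a blocked or permuted list is also computer-generated, and block structure is something an article may leave to the full protocol. This objection stands, and the split probabilities are conditional on it. It does not rescue the comparison itself, which the article does specify and which uses neither period nor pairing.

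**False positives.** A reader might infer that any period shift becomes a false method difference, or that the error rate rises to 9% to 12%. Figures of that size arise at 11:4 with a 1-point shift for an unadjusted paired t-test, which is not the planned test. The Wilcoxon-Mann-Whitney test on paired scores is conservative; in the same setting it gave 2.6% at correlation 0.5 and 0.4% at 0.79 in a separate simulation. Only part of a shift passes through, and random order makes the expected bias zero. This objection also stands.

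**Size of the shift.** The article gives none, and 1 point is nearly the whole 1.1-point target. At half a point the bias at 11:4 is 0.23 and the cost in power is small. Aim 3 is moreover a pilot within an exploratory trial. These points limit how much weight the concern can bear, but the remedy costs almost nothing.

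**One socket or two.** The timeline and adherence sections describe one new socket. If each person wore only one, there would be no period structure. The random-order and analysis sections imply two, and the concern rests on that reading.

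**Conclusion.** The point holds in a limited form. Aim 3 fixes a comparison that discards pairing and period, and the article states no balance between the two orders. If the order is simply randomised, there is a 30% chance of a split that passes at least a third of any period shift into the estimate, and a 12% chance of one that passes nearly half. With an assumed 1-point shift these splits give at least 0.33 and 0.47 points, or 30% and 43% of the 1.1-point target.

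This is bias conditional on the split drawn, together with lost precision. It is not a general inflation of the error rate: at correlation 0.5 the named test clearly exceeds 5% only with a shift of about 2 points and a split of 11:4 or worse. The gain from changing the analysis is substantial under the assumed correlations, but most of it comes from using the pairing rather than from adjusting for period. The shift and the correlations are assumptions; the split probabilities and the shares are exact under simple randomisation.

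**What to change.** 1. Draw the aim 3 order as one permuted list with 8 people in one order and 7 in the other. The statistician holds it and conceals each assignment until enrolment. If the list is already balanced, say so.
2. Keep the named test in its crossover form. Compute each person's first-period minus second-period difference and compare the two order groups with the Wilcoxon-Mann-Whitney test. Estimate the method effect as half the difference between the groups: the expected differences are τ plus a common term in one order and −τ plus the same term in the other, so the common term cancels. Do the same for cost.
3. Reconcile Participant timeline {13} and the adherence section {11c}, which describe one socket, with Implementation {16c} and Statistical methods {20a}, which imply two.

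The cost is one line in the allocation program and one in the analysis text. If there is no period shift, power is slightly lower than with a signed-rank test (about 34% against 39% at correlation 0.5). The last allocation is predictable to anyone who knows the list is 8 and 7.
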